## Abstract

**Background:**

A considerable proportion of patients with mild to moderate traumatic brain injury (TBI) experience long-lasting somatic, cognitive, and emotional symptoms that may hamper their capacity to return to work (RTW). Although several studies have described medical, psychological, and work-related factors that predict RTW after TBI, well-controlled intervention studies regarding RTW are scarce. Furthermore, there has traditionally been weak collaboration among health-related rehabilitation services, the labor and welfare sector, and workplaces.

**Methods/design:**

This study protocol describes an innovative randomized controlled trial in which we will explore the effect of combining manualized cognitive rehabilitation (Compensatory Cognitive Training [CCT]) and supported employment (SE) on RTW and related outcomes for patients with mild to moderate TBI in real-life competitive work settings. The study will be carried out in the southeastern region of Norway and thereby be performed within the Norwegian welfare system. Patients aged 18–60 years with mild to moderate TBI who are employed in a minimum 50% position at the time of injury and sick-listed 50% or more for postconcussive symptoms 2 months postinjury will be included in the study. A comprehensive assessment of neurocognitive function, self-reported symptoms, emotional distress, coping style, and quality of life will be performed at baseline, immediately after CCT (3 months after inclusion), following the end of SE (6 months after inclusion), and 12 months following study inclusion. The primary outcome measures are the proportion of participants who have returned to work at 12-month follow-up and length of time until RTW, in addition to work stability as well as work productivity over the first year following the intervention. Secondary outcomes include changes in self-reported symptoms, emotional and cognitive function, and quality of life. Additionally, a qualitative RTW process evaluation focused on organizational challenges at the workplace will be performed.

**Discussion:**

The proposed study will combine cognitive and vocational rehabilitation and explore the efficacy of increased cross-sectoral collaboration between specialized health care services and the labor and welfare system. If the intervention proves effective, the project will describe the cost-effectiveness and utility of the program and thereby provide important information for policy makers. In addition, knowledge about the RTW process for persons with TBI and their workplaces will be provided.

**Trial registration:**

ClinicalTrials.gov, NCT03092713. Registered on 10 March 2017.

**Electronic supplementary material:**

The online version of this article (doi:10.1186/s13063-017-2218-7) contains supplementary material, which is available to authorized users.

## Background

Successful return to work (RTW) is a major challenge after traumatic brain injury (TBI) [1–6]. Personal factors such as educational level and occupational status, as well as injury-related characteristics, may predict vocational outcome [7–9]. The person’s own perceptions and motivations regarding RTW, as well as aspects of the workplace environment, also have been associated with RTW and work participation after sickness-related absence [10, 11]. Existing literature suggests that the proportion of individuals with TBI who return to work varies from 13 to 85% [7, 8, 12]. Many TBI survivors return to work prematurely and fail to cope with work demands over time once the full impact of the injury is realized. This is probably due to insufficiently coordinated and managed RTW processes and results in low work stability [13].

For many individuals with mild to moderate TBI, it is a major challenge to maintain employment over time while experiencing somatic, cognitive, and emotional symptoms [12, 14]. Impaired executive functioning, learning, memory, and attention are strongly associated with RTW across a variety of disorders affecting brain function and can result in slowness in work performance; difficulties with learning work tasks; distractibility; and problems with planning, organization, and goal-directed behavior. All of these factors may lead to work failure [13, 14]. However, large-scale literature reviews have documented that rehabilitation programs aimed at teaching patients with mild to moderate cognitive problems strategies to manage and compensate for their problems should be a practice standard [15, 16]. Positive work outcomes following cognitive rehabilitation interventions have been reported in studies on moderate to severe TBI [17], but the evidence is insufficient to draw strong conclusions. Compensatory cognitive interventions typically teach clients strategies to compensate for their cognitive deficits in daily living activities, but vocational rehabilitation is rarely addressed specifically in these TBI programs. Authors of a review published in 2009 found that supported employment (SE), based on long-term support and job skills reinforcement through on-the-job coaching, could overcome the limitations of program-based vocational rehabilitation [18]. Furthermore, authors of a systematic review assessing effective RTW interventions found that involvement of patient and employer and work or workplace accommodations were among the components incorporated in the most effective interventions [19].

To date, only a couple of randomized controlled trials (RCTs) have combined cognitive and vocational rehabilitation/SE for patients with mild to moderate TBI [20, 21]. The only study resembling our present protocol was performed by [name] et al. [21, 22]. Their 12-week compensatory cognitive rehabilitation intervention (Cognitive Symptom Management and Rehabilitation Therapy [CogSMART]) was offered in addition to SE for U.S. veterans with mild to moderate TBI. All participants were unemployed but wished to return to work. This group was compared with a control group (CG) that received enhanced SE only. Participants assigned to both SE and CogSMART demonstrated significant reductions in postconcussive symptoms and improvements in prospective memory, but there were no effects on RTW. The authors noted that their study was a pilot in need of replication. Moreover, a process evaluation was not performed in their study, and there are significant differences between the United States and Norway regarding the labor market as well as the welfare system. There is a need to explore different stakeholders’ experiences and processes at the workplace in the RTW process. Finally, there are no RCTs in which researchers have examined the cost-effectiveness of vocational rehabilitation following TBI.

### Approaches, hypotheses, and choice of methods

The present study was based on [name] et al.’s 2014 pilot study that targeted individuals with mild and moderate TBI with persistent cognitive and postconcussive symptoms. The aim of their study was to assess the effect of the CogSMART intervention in combination with SE on improving postconcussive symptoms, neuropsychological performance, quality of life, functional capacity, emotional symptoms, and work participation [21]. Compensatory Cognitive Training (CCT) is a further development of CogSMART [23]. It is a group-based, manualized intervention that includes ten weekly sessions, and it is theoretically based on elements derived from prior cognitive training programs for people with TBI and severe mental illness [21, 23, 24]. The intervention is focused on psychoeducation and compensatory strategy training, and it targets postconcussive symptom management and cognitive symptoms. It is focused on the effect that postconcussive symptoms (such as sleep disturbance, pain, fatigue, headache, tension, and emotional distress) can have on cognitive symptoms and functional recovery. The CCT intervention stresses a biopsychosocial understanding, and it is aimed at educating participants about this complex interrelationship and teaching them stress reduction techniques and strategies to compensate for the functional consequences of the symptoms they are experiencing. The compensatory cognitive strategies target prospective memory, attention and concentration, learning and memory, and executive function [21, 25]. Pilot studies of patients with mild to moderate TBI have demonstrated the efficacy of CogSMART and CCT in improving emotional problems, functional capacity, quality of life, and performance on neurocognitive measures [21–23].

A novel approach to vocational rehabilitation based on the “place-then-train principles” in SE involves support in real-life competitive work settings and is aimed at providing professional services to people with disabilities to help them participate in the competitive labor market [26]. The Five-Step Process describes support activities in the inclusion process: engagement, vocational profiling, job finding, employer engagement, and on-/off-job support. The Individual Placement and Support (IPS) Fidelity Scale is based on eight principles: competitive employment, eligibility based on client choice, integration of rehabilitation and health care services, attention to client preferences, personalized benefits counseling, rapid job search, systematic job development, and time-unlimited and individualized support. SE has not been evaluated in RTW for individuals with TBI in the Norwegian context, but IPS has gained empirical support with positive results in terms of both work inclusion and non-work-related outcomes for people with mental illness [27–29]. SE will be implemented in this RCT in combination with CCT. To determine the feasibility of the proposed interventions and the implementation of procedures in a Norwegian context, a feasibility study will be conducted. In the RCT, the effectiveness of a combined cognitive and vocational rehabilitation intervention compared with treatment as usual (TAU; a nonstandardized rehabilitation provided by a multidisciplinary rehabilitation team) will be evaluated.

The following are the main study hypotheses:Combined CCT and SE will result in a faster RTW and better work stability, as well as reduced postconcussive symptoms and improved cognition, than TAU.Combined CCT and SE will result in reduced emotional distress and improved quality of life compared with TAU.Combined CCT and SE will be a cost-effective alternative compared with the TAU condition.Factors related both to the workplace and to the patient’s motivation for RTW will affect the RTW process.

## Methods/design

### Study design

The proposed study will be a parallel-group RCT with a mixed method in design. Based on the Standard Protocol Items: Recommendations for Interventional Trials (SPIRIT), the study flowchart, standard protocol items, and SPIRIT checklist are provided in Figs. 1 and 2, and Additional file 1, respectively. Once included, participants will undergo a baseline assessment of cognitive and emotional status (T1), with further assessments immediately following the CCT intervention (3 months after study inclusion [T2]), following the end of SE (maximum 6 months after inclusion [T3]), and 12 months after study inclusion (T4). All study assessments will be conducted at Oslo University Hospital (OUH). A process evaluation will be performed to explore participants’ experiences with the intervention, as well as individual and workplace-related mechanisms of importance in the RTW process. A qualitative evaluation study regarding patient experiences with CCT is also being planned.

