### Study interventions

#### CCT-SE intervention

The CCT-SE intervention will comprise a 10-week manualized group intervention that includes weekly CCT group sessions with three to seven participants, which will be provided by a psychologist at OUH. CCT includes psychoeducation, strategy training, and establishment of new habits in several domains. Patients learn about the natural course of postconcussive symptoms and are introduced to sleep hygiene and stress reduction techniques. Compensatory cognitive strategies are taught regarding organization and prospective memory (task management), attention and concentration (during tasks and social interaction), planning and goal setting, learning and memory (internal and external strategies), and executive function (problem solving and self-monitoring). The CCT manual has been translated into Norwegian and adapted to Norwegian conditions in collaboration with the original author of the manual ([name] [21, 42]). The Norwegian user organization (Personskadeforbundet LTN) has participated in the translation process [43].

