The vocational part of the intervention is based on SE principles and will be provided by three trained employment specialists from the NAV Department of Vocational Rehabilitation. For the purpose of this study, the participants will receive vocational intervention for a maximum of 6 months. A main emphasis will be on stages 1 (client engagement), 4 (employer engagement), and 5 (on- and off-the-job support) of the SE Five-Stage Process [38], because all participants will be in regular employment at the time of injury. The initial contact with the participant will be focused on establishing a trustful relationship between the employment specialist and the participant. The employment specialists will use the approach of “discovery,” a process for involving the participant in his/her own RTW process. The next step is mapping the patient’s resources, limitations, and work tasks, as well as establishing common goals between the employment specialist and the participant. The following sessions will be customized to the employee’s needs and may include consultations, guidance and advice, learning/training, work task adaptations, and assistive technology. The sessions may also include the employer and the supervisor at the local NAV office if considered beneficial. The vocational intervention will be integrated with standard Norwegian statutory sick leave follow-up. The International Classification of Health Interventions (ICHI) will be applied for the standardization and documentation of the individualized interventions [44]. ICHI is a tool developed by the World Health Organization for reporting and analyzing health interventions and covers interventions carried out by a broad range of health care providers, including acute care, postacute care, and rehabilitation, as well as assistance with functioning, health prevention, and public health matters. ICHI is still under development, and the last published version is denoted as alpha version 2. The classification will be ready for operational use during the study period.

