### Statistical analysis

Descriptive statistics will be used to describe the baseline and injury characteristics of the variables related to participants and services. The *t* test will be used to analyze between-group mean comparisons for normally distributed continuous data, and the Mann-Whitney *U* tests will be used to analyze skewed data. For the primary outcome measures, a logistic regression model will be used to compare the proportions of participants returning to work at T4 in the CCT-SE and TAU groups, adjusting for other potential confounders. In addition, linear regression analysis will be applied to compare the difference in the mean length to RTW between the intervention groups at T4, adjusting for other potential confounders. For the secondary outcome measures, repeated measures analysis of variance will be used with time (T1–T4) as the repeated-measures factor and group (CCT-SE and TAU) being a between-group factor to test whether the CCT-SE intervention has a beneficial effect compared with TAU on RTW, symptoms, and functioning. The intention-to-treat principle will be applied for all proposed analyses.

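### The article gives T3 two definitions, a fixed 6 months and the end of SE within 6 months; under the second, CCT-SE participants can be assessed earlier than controls

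*Protocol article*

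**What the plan says.** The Study design section of the protocol article sets the third assessment "following the end of SE (maximum 6 months after inclusion [T3"]). The abstract, under Methods/design, sets it "following the end of SE (6 months after inclusion"), with no upper-limit wording.

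The section on the CCT-SE intervention says that "the participants will receive vocational intervention for a maximum of 6 months", and that sessions after the first steps are adapted to the individual. The length of SE therefore varies, and only that arm has an SE end date. For controls, the TAU section states follow-up for 6 months after inclusion.

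The last visit is fixed for everyone: "and 12 months after study inclusion (T4"). For the secondary outcomes, the Statistical analysis section says that "repeated measures analysis of variance will be used with time (T1–T4) as the repeated-measures factor" and that group is the between-group factor.

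**The concern.** A visit defined by the end of a treatment moves with that treatment. If only one arm receives it, the time from inclusion to the visit can differ between arms. That difference arises after allocation, so randomization does not remove it.

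Postconcussive symptoms and quality of life are secondary outcomes at every time point, and improvement in both is among the main hypotheses. If these outcomes change over the months after injury, an arm seen earlier has had less time to recover. An ANOVA indexed by visit label cannot separate elapsed time from the group effect at T3. SE might also end sooner in people who return to work sooner, in which case the shift in timing would depend on outcome. That is plausible, but the documents do not address it.

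**Working it through.** **Step 1: set the texts side by side.**

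| Visit | Abstract | Study design section | Same time since inclusion in both arms? |
|---|---|---|---|
| T2 | 3 months | 3 months | Yes |
| T3 | 6 months | end of SE, at most 6 months | Only under the abstract |
| T4 | 12 months | 12 months | Yes |

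Only T3 differs between the two texts. The article states no figure for the effect of visit timing, so there is nothing of its own to reproduce.

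**Step 2: direction.** Under the literal Study design wording, T3 in the CCT-SE arm can fall before month 6 but not after it. Controls have no SE end, and the only period given for them is 6 months. With recovery over time, the CCT-SE arm would look worse at T3 than it would at month 6. The bias is against the intervention.

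**Step 3: size, for illustration.** Inputs:
- n = 55 per arm, from the Sample size section.
- Two-sided α = 0.05 and no true effect.
- Recovery rate r = 0.02, 0.05 or 0.10 SD per month. This is an assumption.
- CCT-SE seen s = 1, 2 or 3 months before month 6 on average. This is also an assumption.

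Formulas (normal approximation):
- Bias (CCT-SE minus TAU, positive = better) = −r × s.
- Standard error of the standardised difference = √(2/55) = 0.191.
- Chance of falsely favouring TAU = Φ(−1.96 + r·s/0.191).
- Chance of falsely favouring CCT-SE = Φ(−1.96 − r·s/0.191).

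| Shift s (months) | r (SD/month) | Bias (SD) | Falsely favours TAU | Falsely favours CCT-SE |
|---|---|---|---|---|
| 0 | any | 0 | 2.5% | 2.5% |
| 1 | 0.02 | −0.02 | 3.2% | 2.0% |
| 1 | 0.05 | −0.05 | 4.5% | 1.3% |
| 1 | 0.10 | −0.10 | 7.6% | 0.65% |
| 2 | 0.02 | −0.04 | 4.0% | 1.5% |
| 2 | 0.05 | −0.10 | 7.6% | 0.65% |
| 2 | 0.10 | −0.20 | 18.1% | 0.13% |
| 3 | 0.02 | −0.06 | 5.0% | 1.2% |
| 3 | 0.05 | −0.15 | 12.0% | 0.30% |
| 3 | 0.10 | −0.30 | 35.0% | 0.02% |

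These rates apply to a comparison at T3 alone. In a contrast averaged over T2, T3 and T4, a shift at T3 only is divided by three: the 2-month bias of 0.04 to 0.20 SD becomes 0.04/3 = 0.013 to 0.20/3 = 0.067 SD. The neuropsychological tests are not given at T2, so for them the divisor is two: 0.02 to 0.10 SD.

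**Step 4: what is untouched.** The primary return-to-work proportion is analysed at T4, which is 12 months after inclusion for all. Length of time to return to work is counted in days. Neither depends on when T3 takes place.

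**The case against.** **The wording can be read innocently.** The upper limit may describe the cap on SE, as it does in the section on the intervention, with the visit at 6 months as in the abstract. The 6-month follow-up of controls fits that reading. The SPIRIT figure and the flowchart, which are not shown, may also fix the months for both arms. This objection stands in part: the two texts may share one intention. But the Study design sentence as printed allows the other reading, and the two readings lead to different schedules.

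**The size is assumed.** This stands. The article gives neither a recovery rate nor how early SE ends on average. Participants are selected for symptoms persisting at 2 months, so T3 falls about 8 months or more after injury, when recovery may be slow. At 0.02 SD per month the effect of a 2-month shift is small.

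**Windows and visit dates belong in the full protocol or SAP.** This stands for the detail, and the absence of a visit window here is not a finding. The conflict over what T3 is anchored to lies in the printed text.

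**A reader might infer the same problem at T2**, which is described as "immediately following the CCT intervention (3 months after study inclusion [T2"]). The documents do not support this. The abstract agrees on 3 months: "immediately after CCT (3 months after inclusion), following the end of SE (6 months after inclusion), and 12 months following study inclusion". The course is "a 10-week manualized group intervention that includes weekly CCT group sessions with three to seven participants", so it takes 70 days against about 91, leaving about 21 days to start. Waiting for a group to fill does not change the conclusion. If 125 participants are recruited over 12 to 18 months, each arm gains 62.5/18 to 62.5/12 = 3.5 to 5.2 per month. The mean wait, half that of a group's first member, then puts the average end of CCT near day 76–79 for groups of three, 82–87 for five and 88–96 for seven. Only the largest, slowest-filling groups overrun on average, and the stated 3-month anchor does not move with them.

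**A reader might also infer that recovery would be mistaken for benefit.** At T3 the direction is the opposite: an early visit in CCT-SE masks benefit or favours TAU.

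**Conclusion.** The point holds for T3 only. The abstract and the Study design section define T3 differently, and the second definition, taken literally, makes its timing depend on arm while the secondary analysis treats it as common. If outcomes improve with time, the T3 secondary and other outcomes are biased against CCT-SE by 0.04 to 0.20 SD, assuming a mean shift of 2 months and recovery of 0.02 to 0.10 SD per month. The chance of falsely favouring TAU at T3 then rises from 2.5% to between 4.0% and 18.1%. If T3 is in fact held at 6 months in both arms, the bias is zero and only the wording needs repair. The T4 return-to-work comparison and days to return to work are not at risk. The change is worth making because it costs almost nothing and protects the main symptom and quality-of-life comparisons at that visit.

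**What to change.** Reconcile the abstract and the Study design section with one sentence: the T3 assessment takes place 6 months after inclusion in both arms, with the same visit window, whenever SE ends, and the word maximum refers only to the length of SE. The window itself can be set in the full protocol or SAP. This changes the timing of an assessment, not the delivery or length of any treatment.

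The cost is the sentence and one small downside: some CCT-SE participants will be assessed some time after their own SE has ended, so T3 measures status at 6 months rather than status at the end of SE.
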